#### GPBoost models and SHapley additive exPlanations (SHAP) for factor quantification

The GPBoost model, which integrates tree-boosting techniques with Gaussian processes and mixed-effects models, will be used to quantify the impact of various factors on PASC. This model is well-suited for handling complex nonlinearities, discontinuities, and higher-order interactions. Gaussian processes provide the flexibility to model random effects and correlations commonly observed in clinical data. Recursive Feature Elimination (RFE) will be employed to streamline the model by iteratively removing the least significant features, as identified through the GLMM, ensuring focus on the most influential variables. Hyperparameter tuning will be performed using five-fold cross-validation to optimize model settings and improve robustness. The SHAP algorithm will be used to quantify each feature’s contribution to the outcome, providing an interpretable measure of feature importance through mean absolute SHAP values.

#### Causal inference models for risk factors and recovery trajectories

Causal inference models will be used to investigate the complex relationships between risk factors and the development of PASC, as well as the recovery trajectories of affected individuals. These models will aim to identify and quantify causal pathways, offering insights into how various factors influence both the onset and progression of PASC. Variables will be selected based on prior assessments, and longitudinal data will be collected to track changes over time. Directed Acyclic Graphs (DAGs) will be employed to visualize potential causal pathways and identify confounding factors that require control during analysis. Structural equation modeling and propensity score matching will be used to estimate the strength and direction of causal relationships. Sensitivity analyses will ensure the robustness and reliability of the findings.

## Patient and public involvement

Patients and public will not involve in the design, recruitment and conduct of the study.

## Ethics and dissemination

This study adheres to the ethical standards outlined in the Declaration of Helsinki and complies with national and local regulations concerning ethical research practices and patient data protection. The Gansu Provincial Hospital research ethics committee has approved this study protocol (ID: 2024–542), and it is registered as a clinical trial (ChiCTR2400091805). Ethical monitoring and data dissemination will be maintained throughout the study.

Informed consent will be obtained from all participants. For pediatric and geriatric populations, specific considerations include obtaining parental consent for minors and ensuring appropriate consent procedures for seniors, particularly those with cognitive impairments. The study commits to maintaining the confidentiality of all medical information, disclosing it only when required by law and with appropriate consent from involved parties. All clinical research data will be retained for a minimum of 5 years following the completion of the study. Study results will be published in peer-reviewed journals.

## Discussion

This study will employ a longitudinal design to investigate how environmental, socioeconomic, and clinical factors shape PASC outcomes in a demographically diverse population. Comprehensive health data collected during the initial COVID-19 hospitalization help distinguish pre-existing conditions from symptoms emerging as part of PASC. By integrating these clinical records with environmental and socioeconomic variables through mixed-effects models and spatiotemporal analyses, the research provides a comprehensive understanding of how both internal factors (e.g., individual health status, comorbidities) and external factors (e.g., air quality, socioeconomic conditions) influence long-term health outcomes following COVID-19. To ensure a representative sample, the cohort is stratified by age, sex, and initial symptom severity, allowing for a detailed and subgroup-specific analysis of PASC manifestations. This multidimensional approach is essential for uncovering the complex interactions between patient-level susceptibility and broader external influences, ultimately informing targeted strategies to improve the management and mitigation of long-term COVID-19 effects.

Existing literature has widely documented the potential influences of underlying comorbidities, demographic factors, and environmental conditions on PASC outcomes (64). Pre-existing conditions such as cardiovascular disease, diabetes, and chronic respiratory disorders have been shown to exacerbate the severity of PASC symptoms, leading to prolonged recovery and an increased risk of complications (65). Individuals with chronic illnesses are more likely to experience severe acute COVID-19, which may predispose them to long-term sequelae due to sustained systemic inflammation and immune dysregulation (66). For instance, patients with diabetes and obesity have demonstrated heightened susceptibility to persistent inflammatory states post-COVID-19, contributing to ongoing fatigue, dyspnea, and cardiovascular dysfunction (67, 68). By examining how pre-existing health conditions interact with PASC, this study aims to elucidate the mechanisms through which chronic illnesses impact recovery trajectories and to identify potential intervention strategies.

Beyond comorbidities, demographic factors such as gender, education level, and marital status may also influence PASC trajectories (69). Gender differences in immune response and health-seeking behaviors have been linked to variations in symptom persistence and severity, with women more frequently reporting prolonged PASC symptoms, including fatigue, neurological issues, and autonomic dysfunction (70). Additionally, education level and marital status serve as proxies for social support and healthcare access, both of which are critical for managing chronic conditions and facilitating recovery (71). Limited health literacy, often associated with lower education levels, may impact adherence to post-COVID care recommendations, while marital status may influence mental health resilience and access to medical resources (72–74). By incorporating these demographic variables into our analysis, we aim to identify groups with greater susceptibility or resilience to PASC and assess how these interactions affect recovery trajectories.

Environmental pressures, such as air quality, urbanization, and access to green spaces, are increasingly recognized as key determinants of post-COVID-19 health outcomes (15, 20, 75). Air pollution has been linked to increased COVID-19 severity and mortality, and higher exposure to PM2.5 and NO2 has been associated with a higher prevalence of long-term respiratory and cardiovascular symptoms in PASC patients (75). Conversely, access to green spaces has been shown to provide protective benefits, improving mental and respiratory health and facilitating recovery (76). Given the environmental diversity of our study sites, this research will assess how these factors contribute to symptom persistence and recovery, leveraging existing knowledge on environmental determinants of health outcomes to refine analytical approaches and enhance the understanding of PASC progression.

A key strength of this study is its extended follow-up period of up to 48 months post-discharge, allowing for a comprehensive assessment of long-term PASC progression and persistence across different age groups. This prolonged observation provides valuable insights into age-specific recovery patterns, refining predictive models for long-term health outcomes and facilitating the development of targeted interventions. Additionally, the use of Geographic Information Systems (GIS) enhances the study by generating disease distribution maps, which help identify environmental and geographic factors associated with PASC. These insights are not only essential for detecting high-risk areas but also for guiding individualized patient care strategies.

Beyond mapping geographic influences, the integration of environmental and socioeconomic data with clinical outcomes strengthens the understanding of how external factors, such as air pollution, economic disparities, and urbanization, affect the severity and trajectory of PASC. Identifying these factors has direct implications for patient care, enabling healthcare providers to incorporate external influences into personalized treatment plans. Time-series analyses further enhance this approach by tracking temporal trends and evaluating the effects of environmental changes on health outcomes, providing a dynamic perspective on how fluctuating conditions contribute to disease progression. Meanwhile, causal inference models help establish robust causal relationships between environmental, socioeconomic, and clinical variables, ensuring a more rigorous evaluation of COVID-19’s long-term effects on PASC. By combining these analytical techniques, the study offers a multidimensional framework for understanding how environmental and socioeconomic conditions interact with individual health factors, ultimately informing more precise treatment and intervention strategies. This research also carries significant implications for patient care, particularly in identifying specific risk factors that exacerbate PASC in vulnerable populations. By considering both internal and external determinants of health, this study supports a shift toward precision medicine, ensuring that interventions address not only biological vulnerabilities but also environmental and socioeconomic disparities that influence recovery.

Despite the strengths of our study, we acknowledge several limitations and have devised strategies to address them effectively. Firstly, our study is based in Gansu Province, China, involving data from 14 cities, each with unique environmental and socioeconomic characteristics. While this provides a rich dataset within a specific geographic region, it limits broader geographic representation. To address this, we have included multiple sites chosen for their environmental diversity, particularly focusing on urban settings across different regions. This strategic selection helps control environmental factors that could influence health outcomes related to PASC. Secondly, our current study setup does not include direct comparisons with other cities or countries, which restricts our ability to generalize findings across different global environments. We plan to expand our analysis to include such comparisons as comparable data becomes available, allowing for a more comprehensive evaluation of environmental and socioeconomic impacts on PASC rates and health outcomes. Thirdly, the non-random nature of our patient recruitment might introduce selection bias, and the reliance on telephone questionnaires could lead to recall bias, particularly as participants may not accurately remember past symptoms. To mitigate these issues, we use advanced statistical methods to control for potential confounders and perform sensitivity analyses to assess the impact of data attrition. Fourthly, an oversight committee is actively involved in monitoring and evaluating the study’s processes to address any unforeseen issues that arise, thereby ensuring the integrity and validity of our research. Plans for further validation through clinical assessments are in place to enhance the reliability of our findings, particularly to address challenges associated with self-reported data. By implementing these strategies, we aim to refine our understanding of PASC and its diverse impacts across different populations, ensuring that our findings are robust and reflective of the true effects of environmental and socioeconomic factors on health outcomes post-COVID-19.

In conclusion, this research represents a critical advancement in understanding PASC by mapping recovery trajectories and identifying both internal and external factors influencing patient outcomes. The insights gained from this study have the potential to transform precision medicine approaches, allowing for more targeted and effective interventions that address the long-term consequences of COVID-19. Furthermore, these findings will contribute to public health strategies aimed at mitigating the impact of PASC, while also supporting the development of tailored patient care approaches based on individual risk factors.

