## Introduction

Post-Acute Sequelae of SARS-CoV-2 Infection (PASC), commonly referred to as Long COVID, encompasses a broad spectrum of persistent symptoms and medical complications that continue well beyond the initial COVID-19 infection phase (1–6). Symptoms varies widely, ranging from mild, non-specific issues like fatigue and headaches to severe, debilitating conditions including cardiopulmonary abnormalities and significant neurological deficits (7, 8). These manifestations significantly impair quality of life and pose ongoing challenges to global healthcare systems (9).

The risk factors contributing to PASC are not well understood. A complex array of demographic, clinical, environmental, and socioeconomic elements, may influence PASC (10, 11). There is substantial evidence suggesting that the interplay between biological and environmental components, including air quality, temperature, humidity, and pollution levels, significantly impacts respiratory illnesses, including COVID-19 (12–16). These conditions exacerbate respiratory symptoms and increase the risk of severe complications (14, 15). Socioeconomic disparities also play a crucial role, influencing individuals’ vulnerability and resilience to COVID-19 and its prolonged effects (17). Factors such as income inequality, access to healthcare, housing quality, and employment status profoundly affect an individual’s risk of virus exposure and their ability to receive timely and adequate medical care (18). Education level, social support networks, and community resources are pivotal in determining an individual’s capacity to manage and recover from the infection (19).

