## Methods and analysis

### Study population

This prospective cohort study, will enroll over 4000 individuals with RT-PCR-confirmedSARS-CoV-2 at baseline, hospitalized at Gansu Provincial Hospital in China from December 2022 to May 2023 (Gansu PASC dataset). Aligning with methodologies from other PASC research, we will gather comprehensive health data during the patients’ initial hospitalization due to COVID-19 (31). The data collection will include extensive hospital records from their acute COVID-19 admissions, capturing demographic information, clinical data, comorbidities, pre-existing symptoms, and other relevant health details.

The patients were from all 14 cities in Gansu Province (92°13′E-108°46′E, 32°31’N-42°57’N), with various environmental and socioeconomic backgrounds. The municipal geographic coordinates of the 14 cities are detailed as follows: Lanzhou (103°51′E, 36°3’N); Jiayuguan (98°23′E, 39°80’N); Jinchang (102°19′E, 38°52’N); Baiyin (104°14′E, 36°55’N); Tianshui (105°72′E, 34°58’N); Wuwei (102°64′E, 37°93’N); Zhangye (100°45′E, 38°92’N); Pingliang (106°66′E, 35°54’N); Jiuquan (98°49′E, 39°73’N); Qingyang (107°64′E, 35°71’N); Dingxi (104°59′E, 35°61’N); Longnan (104°96′E, 33°37’N); Linxia Hui Autonomous Prefecture (103°21′E, 35°60’N) and Gannan Zang Autonomous Prefecture (102°91′E, 34°98’N). Baseline data will be collected using hospital records, and follow-up assessments will be performed at 24-, 36-, and 48-months post-discharge via structured telephone interviews (Table 1). Exclusion criteria are limited to individuals without available contact details, those who deceased during hospitalization or follow-up, those who declined to participate, and those unreachable for follow-up assessments.

**Table 1 tab1:** Evaluation parameters at baseline and follow-up visits.

Evaluation parameter	Baseline°	Follow-Up°° (telephone interviews)		
	(Hospital admission)	Visit 1 (24 m)	Visit 2 (36 m)	Visit 3 (48 m)
Informed consent	x			
Inclusion criteria met	x			
Demographics*	x			
Environmental/socio-economic factors†	x			
Symptoms‡	x	x	x	x
Life styles¶	x	x	x	x
Vaccination information**	x			
Reinfection††		x	x	x
Recovery condition‡‡		x	x	x
Comorbidities¶¶	x			
Laboratory test results***	x			
Treatment†††	x			
Clinical outcomes	x			
Medical management‡‡‡		x	x	x
Assessment Tools¶¶¶				
EQ-5D-5L score (Adults)	x	x	x	x
mMRC score (Adults)	x	x	x	x
GAD-7 score (Adults)	x	x	x	x
PHQ-9 score (Adults)	x	x	x	x
FSS score (Adults)	x	x	x	x

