ISI score (Adults)	x	x	x	x
EQ-5D-Y (Children 4–15 years)	x	x	x	x
PROMIS (Children 8–17 years)	x	x	x	x
SDQ score (Children 4–17 years)	x	x	x	x

°Baseline Assessment: Conducted at the time of hospitalization for COVID-19 at Gansu Provincial Hospital from 2022 to 2023.

°°Follow-Up Visits: Conducted via structured telephone interviews at three time points from 2024 to 2027.

Visit 1 (24 months post-discharge): PASC diagnosis.

Visit 2 (36 months post-discharge): Long-term outcome assessment.

Visit 3 (48 months post-discharge): Final long-term outcome assessment.

*Demographics: Includes age, gender, ethnicity, marital status (for adults), residential status during infection, education background, personal finances (for adults), work status (for adults), and BMI. These details are tailored to ensure age-appropriateness, with specific personal and professional information omitted for children.

†Environmental/socio-economic Factors: Encompasses sulfur dioxide (SO_2_), nitrogen dioxide (NO_2_), ozone (O_3_), particulate matter 10 (PM_10_), particulate matter 2.5 (PM_2.5_), Normalized Difference Vegetation Index (NDVI), temperature, precipitation, relative humidity, wind speed, per capita GDP, income levels, employment status, job types, education level, and living condition. This comprehensive data helps examine the environmental contexts affecting health outcomes.

‡Symptoms Monitoring: Tracks a wide array of symptoms across various systems.

Respiratory: Difficulty breathing, cough, chest pains.

Digestive: Abdominal pain, diarrhea, nausea, vomiting, loss of appetite, constipation.

Cardiovascular: Palpitations, tachycardia, bleeding.

Musculoskeletal: Arthralgia, myalgia, impaired functioning and mobility.

Nervous System: Headaches, dizziness, “brain fog,” sensory impairments, insomnia, and other sleep difficulties.

Other: Fever, fatigue, skin rashes, irregular menstrual cycles (in females over 12 years of age), erectile dysfunction (in males).

¶Lifestyle Factors: Includes smoking and drinking status, providing insights into behaviors that may influence disease progression and recovery.

**Vaccination Information: Documents the dose and timing of COVID-19 vaccinations, critical for assessing vaccine efficacy and patient immunity.

††Reinfection Data: Tracks instances of SARS-CoV-2 reinfection, including timing and test results (PCR, antigen, self-reported symptoms), to understand immunity and disease dynamics.

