### Outcomes

#### Primary outcome

The primary objective of this study is to assess the persistence and long-term health outcomes of PASC symptoms. The diagnosis of PASC will be formally established during the first follow-up visit to ensure accurate identification and differentiation from pre-existing conditions, while long-term health outcomes will be evaluated at the second and third follow-up visits (Table 1). Our diagnostic protocol follows the criteria outlined in the WHO definition (32), and utilizes structured telephone interviews for initial PASC assessments (33, 34). PASC symptoms typically emerge at least 3 months after the initial SARS-CoV-2 infection and persist for a minimum of 2 months. To ensure an accurate diagnosis, symptoms must not have been present in the 180 days before infection (35). The initial follow-up visit, conducted 12 months post-diagnosis, confirms the presence and persistence of PASC symptoms, which are systematically evaluated across multiple organ systems, including respiratory, digestive, cardiovascular, musculoskeletal, and neurological functions, as well as general symptoms such as fatigue and fever. Symptom severity is quantitatively assessed using a four-point Likert scale to provide a structured and standardized evaluation of PASC’s impact on patient well-being (36, 37). To further validate symptom emergence and progression, our follow-up protocol differentiates post-COVID-19 manifestations from pre-existing conditions. Aligned with established research protocols, our multidisciplinary (MDR) team conducts follow-ups to collect comprehensive data on new diagnoses and medical consultations, allowing for the identification of secondary conditions potentially associated with PASC (38).

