### Statistical analysis

A variety of statistical methodologies will be employed to analyze the primary and secondary outcomes in this study. The data analysis begins with descriptive and inferential statistical methods to identify patterns and establish correlations. Continuous data will be presented as means with standard deviations (SD), while categorical variables will be reported as percentages. For comparisons across groups, analysis of variance (ANOVA) will be used for continuous variables, and chi-square tests for categorical variables, both with Bonferroni corrections applied in post-hoc analyses. A significance level of *p* < 0.05 will be consistently applied, with adjustments made for multiple comparisons to enhance the reliability of results. Logistic regression models will be employed to evaluate the impact of multiple factors on the severity of PASC. We will utilize a multivariable logistic regression model to analyze the relationship between various independent variables, including demographic factors, clinical characteristics, and environmental exposures, and the binary outcome of PASC presence or absence. The model will integrate variables selected based on clinical relevance and statistical significance derived from preliminary univariate analyses, ensuring that only factors significantly associated with the outcome are included in the final analysis. Variables for inclusion will be chosen based on their potential impact on PASC, informed by both clinical judgment and empirical evidence from initial analyses. We plan to investigate interaction terms, particularly between key demographic and clinical variables, to explore complex interactions that may affect PASC risk. Model fit will be assessed using the Hosmer-Lemeshow test for goodness-of-fit and Receiver Operating Characteristic curve analysis to evaluate predictive accuracy. We will also employ validation techniques such as split-sample validation or cross-validation to confirm the model’s robustness. Sensitivity analyses will be conducted to examine the stability of our results under various assumptions regarding data missingness and potential measurement errors, ensuring that our findings are reliable and applicable across different scenarios. Additionally, advanced analytical techniques will complement these methods, utilizing R (version 4.3.0) with the ‘gpboost’ and ‘stats’ packages and Python (version 3.10) with ‘sklearn’ and ‘gpboost.’

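### Causal claims about environment and PASC, and about the long-term effects of COVID-19, go beyond what an all-infected cohort can identify

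*Protocol article*

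**What the plan says.** All references are to the protocol article.

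- **Cohort.** The Study population section "will enroll over 4000 individuals with RT-PCR-confirmedSARS-CoV-2 at baseline", all hospitalised at one hospital. No uninfected or pre-pandemic group is described.
- **Outcome.** The Statistical analysis section models "the binary outcome of PASC presence or absence". Primary outcome gives the timing rule: "PASC symptoms typically emerge at least 3 months after the initial SARS-CoV-2 infection and persist for a minimum of 2 months". It also requires that symptoms were absent in the 180 days before infection. Table 1 lists about 25 symptoms, three of them respiratory.
- **When PASC is diagnosed.** Table 1 and Follow-up assessments place it at Visit 1, 24 months after discharge. Primary outcome places the first visit 12 months after diagnosis.
- **Environment and symptoms.** Of air quality, temperature, humidity and pollution, the Introduction says: "These conditions exacerbate respiratory symptoms and increase the risk of severe complications".
- **Causal claims.** The causal inference section plans structural equation modelling and propensity score matching to estimate the strength and direction of causal relationships with PASC onset and recovery. The Discussion goes further: "Meanwhile, causal inference models help establish robust causal relationships between environmental, socioeconomic, and clinical variables". The same sentence promises a more rigorous evaluation of the long-term effects of COVID-19.
- **Limitations.** The only missing comparison acknowledged is geographic: "our current study setup does not include direct comparisons with other cities or countries". Selection, recall, attrition and self-report are also covered. The absence of an uninfected comparator is not.

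**The concern.** A person who develops a lasting cough a year after discharge, for reasons unrelated to COVID-19, meets every stated criterion: onset more than 3 months after infection, duration over 2 months, absent in the 180 days before. That person is counted as having PASC. If such symptoms are commoner where the air is worse, an environmental association with 'PASC' appears even when environment has no bearing on what the infection left behind.

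The planned models compare infected people with other infected people. Adjustment, matching and path models can address confounding of exposure. They cannot estimate the background rate, because infection status does not vary. For the same reason the cohort cannot evaluate what COVID-19 itself contributes.

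The study intends to inform targeted PASC interventions. If part of an environmental association reflects background illness, the conclusion that environment shapes PASC would be misdirected to that extent.

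**Working it through.** The article gives no effect size, power or background symptom rate, so there is no figure to reproduce. The first step is a check of identification; the second is an illustration on assumed rates.

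**1. What the safeguards cover.**

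- 180-day rule and baseline hospital records: symptoms present before infection. New background symptoms are not covered.
- Onset and duration rule: early and transient symptoms. New persistent background symptoms are not covered.
- Collection of new diagnoses and consultations: used to identify conditions possibly associated with PASC. The article states no rule for excluding other causes.
- Mixed models, GPBoost, propensity scores, structural equation models: differences among infected people. They carry no information on symptom rates without infection.

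**2. Possible size.** Let *c* be the risk of an infection-attributable symptom, set equal at low and high exposure, so there is no environmental effect on it. Let *b* be the risk of a new background symptom by Visit 1, which differs by exposure. If the two arise independently,

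observed 'PASC' p = 1 − (1 − c)(1 − b), and OR = [p_high/(1 − p_high)] / [p_low/(1 − p_low)].

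Example: c = 0.20, b = 0.10 v 0.15.
p_low = 1 − 0.80 × 0.90 = 0.28; p_high = 1 − 0.80 × 0.85 = 0.32.
OR = (0.32/0.68)/(0.28/0.72) = 1.21.

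All values of *b* and *c* below are assumptions:

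| c | b low v high | observed 'PASC' | OR |
|---|---|---|---|
| any | equal | equal | 1.00 |
| 0.30 | 0.10 v 0.12 | 37.0% v 38.4% | 1.06 |
| 0.10 | 0.10 v 0.12 | 19.0% v 20.8% | 1.12 |
| 0.30 | 0.10 v 0.15 | 37.0% v 40.5% | 1.16 |
| 0.20 | 0.10 v 0.15 | 28.0% v 32.0% | 1.21 |
| 0.10 | 0.15 v 0.20 | 23.5% v 28.0% | 1.27 |
| 0.10 | 0.10 v 0.15 | 19.0% v 23.5% | 1.31 |
| 0.10 | 0.15 v 0.25 | 23.5% v 32.5% | 1.57 |

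**3. Chance of a significant result.** Take the 1.21 example with 2,000 v 2,000 independent patients and two-sided alpha 0.05 (the article gives 0.05 but not the sidedness). The standard error is √(2 × 0.30 × 0.70/2000) = 0.01449 under no difference and √((0.28 × 0.72 + 0.32 × 0.68)/2000) = 0.01448 under the assumed rates. Then (0.04 − 1.96 × 0.01449)/0.01448 = 0.80, a chance of about 79%. It is 57% if 2,400 in total are followed. For b = 0.10 v 0.12 the chance is only 15% to 30% across c = 0.30 to 0.10. Clustering in 14 cities would lower all these chances without removing the bias.

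**4. What a comparator would add.** If *b* were known at each exposure level, c = 1 − (1 − p)/(1 − b). In the example, 1 − 0.72/0.90 = 0.20 and 1 − 0.68/0.85 = 0.20, so the environmental effect on infection-attributable symptoms is correctly zero. The infected cohort supplies *p* but not *b*.

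**The case against.** **The claim is mostly rhetoric.** The Abstract speaks of exploring correlations, the primary objective is persistence and long-term outcomes, and the causal section says its models will aim to identify pathways. Predictors of symptoms among infected survivors are a legitimate target. This stands: the planned models need not change. But the causal section and the Discussion are current text and state more than the cohort can deliver.

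**The outcome is tighter than any new symptom.** The article invokes the WHO definition, a multidisciplinary team and planned clinical validation. These may reduce the background that is counted. They do not measure how much remains or whether it varies with exposure.

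**The exposure is short-term.** Environmental data assigns monthly meteorology and pollution by place and admission period, and a city random intercept is planned. The illustration assumes a sustained contrast, so it does not model the planned analysis. That limits what the odds ratios can be taken to predict, not the identification argument.

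**Stronger readings the documents do not support.**

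- A reader might infer that the article concedes that pollution and climate cause all the listed symptoms without COVID-19. The Introduction speaks only of respiratory illness and symptoms, and of worsening them. For insomnia, joint pain or constipation the link is an assumption.
- A reader might infer that any environmental finding would be wholly background. Nothing in the article fixes the size; it could be small.
- A reader might add the Table 1 note that vaccination data are "critical for assessing vaccine efficacy and patient immunity". That concerns selection on infection and hospitalisation, a different problem, and no vaccine-efficacy analysis is described.

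**Conclusion.** The point holds for the claims, not for the cohort as such. With all participants infected, and criteria that exclude only pre-existing symptoms, the study can estimate associations with new persistent symptoms among hospitalised COVID-19 survivors. It cannot show that an environmental or socioeconomic effect is specific to PASC, and it cannot evaluate the long-term contribution of COVID-19. The limitations paragraph does not say so.

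On the assumed rates the spurious odds ratio is about 1.06 to 1.57, and 1.00 if background symptoms do not vary with exposure. This rests on independence of the two symptom sources, equal infection-attributable risk across exposure, and a sustained exposure contrast. It shows what is possible; it is not an estimate for Gansu. The lack of identification does not depend on these figures.

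**What to change.** 1. In the causal inference section and the Discussion, state the estimand as the association of environmental and socioeconomic factors with new persistent symptoms among hospitalised COVID-19 survivors.
2. In the Discussion, remove the assertion in "Meanwhile, causal inference models help establish robust causal relationships between environmental, socioeconomic, and clinical variables" and the linked promise to evaluate the long-term effects of COVID-19, as properties of this design.
3. Add the missing uninfected comparator to the limitations, as a limit on PASC-specific conclusions.
4. Reconcile the timing of the first visit (12 months after diagnosis v 24 months after discharge), since it sets the window in which background symptoms can accrue.

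Optionally, the same models could be fitted to symptoms before infection, since baseline records are described as "capturing demographic information, clinical data, comorbidities, pre-existing symptoms, and other relevant health details". This should be reported as an exploratory check only, and only if those data prove complete. A full pre-infection symptom inventory is not shown. The check would set prevalence in hospital records against incidence by telephone, in different risk sets, with admission-period exposures that follow the symptoms. It cannot serve as a rule for calling an association PASC-specific.

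The cost is wording, plus one set of model fits if the optional check is run. The downside is more modest conclusions.
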